## Randomisation

Patients are randomly allocated to the group ‘new diagnostic strategy’ or the group ‘current diagnostic strategy’, on the day of the LDI scan. Stratification will be performed for the three different centers and the severity of the burns: total burned surface area ≤10% or >10%. A randomisation list is prepared for each stratum on the principle of random permuted blocks of patients, using a random number table [29]. The allocation sequence is concealed by using sequentially numbered, opaque sealed envelopes (SNOSE) prepared by the coordinating researcher ([name]) which are opened at day of LDI after having obtained informed consent, by one of the local researchers [30].

The care provider, outcome assessor and patients are blinded to the results of the LDI in the group ‘current diagnostic strategy’. However, they are not blinded to the group in which patients are randomised.

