**Methods/design:**

A multicenter randomised controlled trial will be conducted in the Dutch burn centres: Beverwijk, Groningen and Rotterdam. All patients treated as outpatient or admitted to a burn centre within 5 days post burn, with burns of indeterminate depth (burns not obviously superficial or full thickness) and a total body surface area burned of ≤ 20% are eligible. A total of 200 patients will be included. Burn depth will be diagnosed by both clinical assessment and laser Doppler imaging between 2–5 days post burn in all patients. Subsequently, patients are randomly divided in two groups: ‘new diagnostic strategy’ versus ‘current diagnostic strategy’. The results of the LDI-scan will only be provided to the treating clinician in the ‘new diagnostic strategy’ group. The main endpoint is the effect of LDI on wound healing time.

In addition we measure: a) the effect of LDI on other patient outcomes (quality of life, scar quality), b) the effect of LDI on diagnostic and therapeutic decisions, and c) the effect of LDI on total (medical and non-medical) costs and cost-effectiveness.

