### Intervention

We will include a total of 200 patients and randomly divide them in two groups: new diagnostic strategy versus current diagnostic strategy. In the first few days the burns will be treated with regular topical antimicrobials or dressings. LDI is performed between 48 hours and 5 days post burn in this study. After removal of the topical agent (during regular wound care), all wounds of indeterminate depth are scanned by a trained research physician or nurse, who is not involved in the patient treatment. In case of clearly superficial wounds next to intermediate wounds in a study patient, the superficial wounds will not be scanned; similar to what would happen in daily practice.

Results of LDI are (Figure 1): [12]

• Red/pink represents a healing potential within 14 days post burn

• Yellow/green represents a healing potential between 14–21 days

• Blue represents a healing potential > 21 days

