### Outcomes

#### Primary outcome measure: wound healing time

Wound healing time is defined as the number of days between LDI (randomisation) and the day on which reepithelialisation of >95% is achieved. Next to that, for generalisation and LDI accuracy checks, we will present the time to wound healing from the day of injury. During wound care an experienced burn specialist will assess reepithelialisation; this is a reliable and valid technique (compared to digital image analysis) [16]. Wounds in admitted patients are assessed daily and wounds in outpatients two or three times a week. Differences in wound healing time between the two randomisation groups will be analysed.

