#### Secondary outcomes measures

##### Quality of life and scar quality

Quality of life will be measured as soon as possible after injury to determine pre-injury functioning (at least within one month post burn) and after 3 months with the EuroQol-6D (EuroQol-5D + cognitive functioning; validated in patients aged ≥ 5 years) or the ItQol-47 questionnaire (validated in children < 5 years of age) [17-19].

The EuroQol-5D questionnaire can result in 243 different health states, which can be converted in a summary (utility) score between 0 (death) and 1 (perfect health) [18]. The EuroQol (EQ-5D) is an extensively used general health questionnaire to measure quality of life. It is recommended for the assessment of HRQoL in injury patients, especially for economic assessments [20].

Scar quality will be measured 3 months post-injury. Scar quality will be measured as follows;

• Elasticity will be measured with the Cutometer® Skin Elasticity Meter 575 (Courage and Khazaka Electronic GmbH, Cologne, Germany) The cutometer provides several elasticity parameters. In this study, maximal skin extension (Uf) (in mm) will be used, because this has been demonstrated to be the most reliable parameter [21].

• Vascularity and pigmentation will be measured with the Dermaspectometer, which is a reliable narrowband spectrometer that computes an erythema and melanin index (Cortex Technology, Hadshund, Denmark) [22].

• Subjective scar assessment will be performed by means of the Patients Observer Scar Assessment Scale (POSAS), a reliable and valid scar assessment tool that consists of a patient and observer scale [22,23]. The patient scores the scar characteristics colour, pliability, thickness, relief, itching and pain. The observer scale contains the items vascularisation, pliability, pigmentation, thickness, and relief. All items are scored numerically on a 10-point rating scale. In addition, the two observers and the patient give a general opinion on the scare quality on a 10-point rating scale.

Differences in quality of life and scar quality 3 months post burn between the two diagnostic groups will be analysed.

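### Patients and outcome assessors are left aware of the randomised group, although both arms are scanned and only the clinician deciding on treatment needs to know it

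*Protocol article*

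**What the plan says.** The abstract (Methods/design) gives the scan to everyone: "Burn depth will be diagnosed by both clinical assessment and laser Doppler imaging between 2–5 days post burn in all patients". It then states what separates the arms: "The results of the LDI-scan will only be provided to the treating clinician in the ‘new diagnostic strategy’ group". Under Intervention, the wounds are "scanned by a trained research physician or nurse, who is not involved in the patient treatment".

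The Randomisation section has a local researcher open the envelope on the day of the scan. It keeps the scan result of current-strategy patients from the care provider, the assessor and the patient, but says that "they are not blinded to the group in which patients are randomised".

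Two sections describe the outcomes that depend on judgement:

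- **Primary outcome.** "During wound care an experienced burn specialist will assess reepithelialisation". The endpoint is the day on which more than 95% is healed. Inpatients are assessed daily and outpatients two or three times a week. The article describes the method as reliable and valid against digital image analysis.
- **Scar quality and quality of life at 3 months.** The POSAS has a patient scale and an observer scale, and "the two observers and the patient give a general opinion on the scare quality". Quality of life comes from questionnaires. Elasticity, vascularity and pigmentation are measured with instruments.

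The article gives no reason for leaving the group open, and its Discussion does not list this among the limitations.

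**The concern.** Many trials of a visible intervention cannot mask patients. In this one the visible procedure is the same in both arms, so the scan does not reveal the group. The protocol already has an information barrier, since it withholds the scan result in the control arm. It stops short of withholding the group label from people who make no treatment decision.

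A patient or scar observer who knows that the new device guided care may score more favourably, and a rater who knows the arm may call a wound healed at an earlier visit. These data also feed the economic evaluation. Healing time is the denominator of the main cost-effectiveness ratio, and the EuroQol answers supply the QALYs. A bias would therefore carry into the adoption decision that the trial is meant to inform.

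**Working it through.** No figure in the plan depends on blinding, so the main check is to ask, for each role, whether the trial needs that person to know the group.

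| Role | Needs the group? | Can it be withheld? |
|---|---|---|
| Clinician deciding on treatment | Yes: receives, or does not receive, the scan result | No |
| Person scanning | No treatment role | Not an outcome rater as described |
| Patient or parent | No: scanned in either arm | Yes, though treatment may give hints |
| 3-month POSAS observers, instrument operators | No | Yes |
| Burn specialist judging healing | Not for the rating itself | Unclear: the article does not say whether this is the treating clinician |

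The case is clear for patients and scar observers. For the healing call it depends on staffing that the article does not describe.

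**Sensitivity of the healing endpoint (illustration).** Inputs from the Sample size section: SD 5 days, target effect 2.25 days, two-sided α 0.05, and 190 patients before dropout, so 95 per arm. Two cautions apply to these inputs. The 190 does not follow from them: 2 × (1.960 + 0.842)² × 5² / 2.25² = 77.5, so 78 per arm and 156 in total. The 2.25 is printed as 57.5% × 5.3, which is 3.05, whereas 42.5% × 5.3 = 2.25. Neither affects the blinding point. I use 95 per arm and 2.25 days as printed.

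Standard error of a difference in means: 5 × √(2/95) = 0.73 day.

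Chance of a significant result with no true effect and a spurious shift b: 1 − Φ(1.96 − b/0.7255) + Φ(−1.96 − b/0.7255).

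| Assumed shift b (days) | b / 2.25 | Chance of p < 0.05 |
|---|---|---|
| 0 | 0% | 5% |
| 0.5 | 22% | 11% |
| 1.0 | 44% | 28% |
| 1.5 | 67% | 54% |

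A noncentral t calculation gives 10.5%, 27.8% and 53.9%, the same after rounding.

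The visit schedule shows how such a shift could arise. Two or three visits a week are 7/2 = 3.5 or 7/3 = 2.3 days apart. If 20% of one arm were called healed one visit early, the arm mean would move by 0.20 × 2.3 = 0.47 to 0.20 × 3.5 = 0.70 day. This applies to outpatients. For inpatients one assessment is one day.

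The shift is my assumption in every row, and the planned comparison is a log-rank test, not a comparison of means. For the POSAS and quality of life the article gives no SD or target difference, so no size can be computed for the outcomes that the fix protects best.

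**The case against.** Open allocation is stated plainly. It is a design choice in a trial of introducing a device into practice, not an error or a contradiction. Several objections have force.

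- **Healing is judged during wound care.** The specialist may be the clinician who holds the scan result, and therapeutic decisions are followed until healing, so the team is exposed throughout. A reader might infer that blinding the primary outcome would need no extra staff. The article does not support that: it does not say who is available, and a masked reading might need a separate assessor.
- **Treatment can hint at the arm.** The Background expects earlier excision and grafting with the scan. It would be too strong to say that nobody could tell the group unless told. A patient would also have to remain unaware that a scan result had guided the decision on surgery.
- **The rejection rates are not findings.** A reader might take 28% or 54% as the trial's false-positive rate, or as the gain from the fix. They are neither. They rest on assumed shifts and concern the outcome that the cheap changes help least. A full-day mean shift would need consistent misdating, since inpatients are seen daily. The direction is also assumed: the Discussion expects clinicians to rely less on the scan at first.
- **Not every outcome is a judgement.** The Cutometer and Dermaspectometer are instruments and are less exposed.
- **Recruitment began in December 2011**, so a change would mix masked and unmasked patients.

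The stated reliability and validity of the healing assessment is a weaker objection. Agreement with image analysis does not protect against a rater who knows the arm. None of these points gives a reason to disclose the group to patients or to scar observers.

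**Conclusion.** The point holds in a limited form. The protocol leaves patients and outcome assessors aware of the group without stating a reason, in a design where identical scanning makes much of that avoidable. The POSAS patient and observer scores and the quality-of-life answers carry the clearest avoidable risk. The healing date carries some risk too, but how much of it can be removed depends on whether the assessor is separate from the treating clinician, which the article leaves open.

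The size of the bias is unknown. The illustration shows only that the healing endpoint is sensitive: half a day of differential dating, 22% of the target effect, would roughly double the 5% error rate. This does not show that the result would be biased or that the primary analysis is invalid. The change is worth making because it is cheap, and unblinded healing assessment should be reported as a limitation in any case.

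**What to change.** Amend the Randomisation section so that, on the clinical side, the allocation and the scan result go only to the clinician deciding on treatment. Specifically:

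1. Do not disclose the group to patients or parents.
2. Keep the existing 3-month POSAS observers and the instrument operators unaware of the group.
3. Keep the allocation off the wound-care sheet, and put the scan result on a separate sheet.
4. For each healing call, record whether the assessor knew the group. Have the call made by an existing specialist unaware of it where this needs no added staff.
5. Report unblinded healing assessment as a limitation, and report how many calls were made with the group known.

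The cost is a protocol amendment, an instruction to three sites, a separate result sheet and a tick-box. Masking will be partial: early surgery may hint at the arm, one clinician may both decide on treatment and judge healing, and patients enrolled before the change are unblinded. The date of the change should be recorded so that patients enrolled before and after it can be told apart.

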## Statistical analysis

Data will be primarily analysed according to the intention-to-treat principle. We assume that time to LDI will be equal in both diagnostic groups, as a result of randomisation. Thus, the differences in effects (e.g. time to wound healing) and costs will be assessed from randomisation onwards.

Differences in time to wound healing (numbers of days between LDI and day of > 95% reepithelialisation) and timing of surgery in both diagnostic strategy groups will be analysed with Kaplan-Meier curves and log rank test.

Quality of life (derived from the ItQol-47 and EuroQol-6D), scar quality (assessed by the Cutometer®, Dermaspectometer® and POSAS) and length of hospital stay will be analysed using the independent-sample-t-test (in case of normal distribution) or the Mann–Whitney test (non-normal distribution).

Differences in diagnostic and therapeutic decisions will be analysed with the Chi-square test. Diagnostic accuracy will be assessed by calculating sensitivity and specificity of the LDI compared to the reference test: time to wound healing (in conservative treated patients) or biopsy (in surgical treated patients). In addition, receiver operating characteristic (ROC) curves will be calculated for both diagnostic groups.

Differences in mean costs (after randomisation) will be analysed by the Mann–Whitney test, since healthcare costs are typically highly skewed. Non-parametric techniques (bootstrapping) will be used to derive a 95% confidence interval for the differences in distributions of the costs.

The cost-effectiveness analysis and cost-utility analysis are performed by dividing the differences in average costs by the differences in average effects or utility. In a sensitivity analysis, the impact on cost-effectiveness of statistical uncertainty on the main study outcomes will be determined (uni- and multivariable).

Data analysis will be performed using SPSS-software (Statistical Package for the Social Sciences).

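### The primary log-rank test counts from a scan on day 2 to 5 post burn without adjusting for that day: no bias, but a small and avoidable loss of precision

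*Protocol article*

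**What the plan says.** All references are to the protocol article.

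- **Primary outcome measure: wound healing time.** The clock starts at the scan: "Wound healing time is defined as the number of days between LDI (randomisation) and the day on which reepithelialisation of >95% is achieved". A second clock will also be reported: "for generalisation and LDI accuracy checks, we will present the time to wound healing from the day of injury".
- **Intervention.** The scan has a window: "LDI is performed between 48 hours and 5 days post burn in this study".
- **Randomisation.** Allocation takes place "on the day of the LDI scan", so the interval from burn to scan is fixed before allocation. The stratification factors are centre and burned surface area: "Stratification will be performed for the three different centers and the severity of the burns: total burned surface area ≤10% or >10" per cent. Scan day is not among them.
- **Statistical analysis.** The premise is "We assume that time to LDI will be equal in both diagnostic groups, as a result of randomisation", and the article concludes from it that effects and costs are to be assessed from randomisation. Time to healing "will be analysed with Kaplan-Meier curves and log rank test". No stratification or covariate is named.
- **Economic evaluation.** The cost-effectiveness ratio divides by the difference in healing time, again measured from randomisation.

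**The concern.** Part of the time to healing has already passed when the clock starts, and that part differs between patients. Two burns that both heal on day 13 score 11 days if scanned on day 2 and 8 days if scanned on day 5. If healing day post burn does not depend on scan day, this difference says nothing about treatment. It adds variance to the primary outcome, and any chance difference between arms in mean scan day passes day for day into the difference in mean healing time.

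The stated premise holds only in expectation. It justifies randomisation as an unbiased time origin, but it does not make scan day equal in one trial of 200 patients or remove its spread within arms. At stake are some precision in the primary test and in the denominator of the cost-effectiveness ratio, and an avoidable argument if the arms happen to differ in scan day.

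**Working it through.** **Inputs from the Sample size section:** difference 2.25 days, SD 5 days, two-sided α 0.05, power 0.80, 190 patients before dropout (95 per arm, taking 1:1). Case mix: 57.5% conservative, healing at about day 13; 42.5% surgical, healing at day 19, with an expected reduction of 5.3 days.

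**The plan's own figure.** n per arm = 2(1.96 + 0.84)² × 5² / 2.25², which gives 78, or 156 in total (158 with the t distribution). The stated 190 is not reproduced; it would need an SD of about 5.5. That is a separate matter and errs on the safe side. The 2.25 days equals 42.5% × 5.3 = 2.2525, whereas the article prints 57.5%.

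**Assumptions.** The scan-day distribution is not given, so three are tried. Healing day post burn is taken as independent of scan day, and the SD of 5 as the SD on the injury clock. The article does not say which clock the SD refers to, although the surgical mean of 19.0 days is built from a time post burn.

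**Formulas.** With V the variance of scan day:
- total variance = 25 + V; share = V / (25 + V)
- SE of the difference in mean scan day = √(2V/95); 95% range = ±1.96 × SE
- power at 95 per arm from the two-means formula with SD √(25 + V)

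| Scan day | V | Share | Total SD | 95% range of imbalance | Power, two means |
|---|---|---|---|---|---|
| no spread | 0 | 0% | 5.00 | 0 | 0.873 |
| continuous uniform, 2 to 5 | 9/12 = 0.75 | 2.9% | 5.07 | ±0.25 day | 0.863 |
| days 2, 3, 4, 5 equally likely | 1.25 | 4.8% | 5.12 | ±0.32 day | 0.857 |
| half day 2, half day 5 (maximum) | 2.25 | 8.3% | 5.22 | ±0.43 day | 0.844 |

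Against the target, the imbalance range is 0.25/2.25 = 11% to 0.43/2.25 = 19%.

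**The planned test.** The two-means formula is not the log-rank test, so log-rank power was simulated (95 per arm, 2,500 trials) under two models. Model A: normal healing times with SD 5 and a shift of 2.25 days for the whole arm. Model B: the protocol's case mix, with 5.3 days gained in surgical patients only and a within-group SD of √(25 − 0.425 × 0.575 × 6²) = 4.03.

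| Model and scan days | From scan, unadjusted | From scan, stratified by scan day | From injury |
|---|---|---|---|
| A, equally likely | 78.9% | 80.3% | 80.9% |
| A, half day 2, half day 5 | 78.2% | 81.0% | 81.6% |
| B, equally likely | 96.0% | 96.4% | 97.0% |
| B, half day 2, half day 5 | 95.2% | 96.9% | 97.2% |

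A repeat gave 78.4% against 80.0% and 77.1% against 80.4% for the two rows of model A (unadjusted against stratified), and a gain of under 1 point for the case mix. At 80% power the simulation error of each figure is about √(0.8 × 0.2/2,500) = 0.8 point, so gains below a point should not be over-read. Type I error was near 5% for every version (4% to 6.5% over all runs). The power level depends heavily on the model; the gain from stratifying does not, at about 0 to 3 points.

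**The case against.** The strongest reply is that nothing here is wrong. Scan day is fixed before allocation, so it is balanced in expectation and the quoted assumption is sound in that sense. Randomisation is the usual origin for an intention-to-treat comparison, and it excludes the days when the LDI result could not yet act. Chance imbalance in a baseline variable is already part of ordinary sampling error. All of this stands.

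A reader might infer that up to 3 days of timing noise enters a 2.25-day comparison. The documents do not support that. Three days is the range for a single patient, while 2.25 days is a difference between arm means. The comparable quantity is the imbalance in mean scan day, at most about ±0.43 day. Nor does the plan ignore scan day, since time from injury will be presented. It only does not adjust for that day in the primary test.

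The size also rests on unstated inputs. The trial's mechanism is that the scan prompts earlier surgery; to the extent that surgery and healing follow the scan, the scan clock adds less noise than computed. If the SD of 5 already includes scan-day spread, nothing is lost against the plan. Removing that spread would then still raise two-means power from 0.873 to between 0.883 and 0.902.

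Lastly, a condensed article may leave covariates to the full protocol or analysis plan. That would dispose of a complaint about missing detail. But this article states its test and gives equal time to LDI as its reason for counting from randomisation, so a comment on the stated method is fair.

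**Conclusion.** The point holds as a minor matter of precision. The time origin is legitimate, and the comparison is unbiased with its error rate intact. What remains is that a recorded, pre-randomisation variable adds about 3% to 8% of the outcome variance, allows a chance imbalance of about ±0.25 to ±0.43 day, and costs about 0 to 3 points of log-rank power, none of which the stated primary test addresses. The figures assume a scan-day distribution between continuous uniform over days 2 to 5 and an even split between days 2 and 5, healing day post burn independent of scan day, and an SD of 5 on the injury clock. They are upper figures where the last two assumptions fail. The trial's conclusions do not hang on this.

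**What to change.** In Statistical analysis, keep randomisation as the time origin and add that the primary log-rank test is stratified by days from burn to scan (2, 3, 4, 5). State that the mean difference in healing time used in the cost-effectiveness ratio is adjusted for the same variable. Reword the premise to say that randomisation balances time to LDI in expectation. The planned presentation of time from injury can stay as it is.

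The cost is a sentence or two. No new data are needed, because counting healing from both the scan and the injury already requires both dates. If centre and burned surface area are also to enter as strata, there would be 3 × 2 × 4 = 24 cells, or about 200/24 ≈ 8 patients each. A Cox model with scan day as a covariate would then be the more practical form. Either choice should be fixed before outcomes are compared by arm.

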### Participants

All consecutive patients of any ages with acute burns of indeterminate depth (assessed by the treating clinician), who are seen within 5 days post burn at one of the three burn centres, are eligible.

Inclusion criteria:

• Patients with acute burns of indeterminate depth (=intermediate depth; the burn wound is not obviously superficial or obviously full thickness)

• Outpatient treatment or admission in one of the three Dutch burn centres

• Presentation within 5 days post burn

Exclusion criteria:

• The presence of full thickness wounds, next to intermediate wounds

• Topical treatment/dressings that impair scanning (e.g. hydrocolloid dressings)

• Patients with peri-orbital facial burns, in which the eyes are unable to shield

• Patients or their next of kin if they are under aged or temporary incompetent who can not be expected to give informed consent e.g. because of cognitive dysfunction or poor Dutch proficiency.

• Patients with a TBSA burned > 20%

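### Length of stay and costs are compared without adjusting for whether the patient was an inpatient or outpatient at randomisation, which gives up precision but not validity

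*Protocol article*

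**What the plan says.** - **Who is enrolled (Participants).** Both care settings qualify: "Outpatient treatment or admission in one of the three Dutch burn centres".
- **When allocation happens (Randomisation).** Patients are allocated "on the day of the LDI scan", which the Intervention section places between 48 hours and 5 days post burn. Effects and costs are counted from that day.
- **Stratification (Randomisation).** "Stratification will be performed for the three different centers and the severity of the burns", the latter split at 10% burned surface area. Care setting is not a factor.
- **Length of stay (Statistical analysis).** "length of hospital stay will be analysed using the independent-sample-t-test (in case of normal distribution", or the Mann–Whitney test if not normal.
- **Costs (Statistical analysis).** "Differences in mean costs (after randomisation) will be analysed by the Mann–Whitney test, since healthcare costs are typically highly skewed". In addition, "Non-parametric techniques (bootstrapping) will be used to derive a 95% confidence interval for the differences in distributions of the costs".
- **Ratios (Statistical analysis).** The cost-effectiveness and cost-utility analyses are "performed by dividing the differences in average costs by the differences in average effects or utility".
- **Cost build-up (Economic evaluation).** Hospital-day cost is length of stay times a day price. Total cost also covers dressings, surgery, outpatient visits, other healthcare, travel and productivity loss.

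No covariate is named for any of these comparisons. The only sub-analysis, in the Discussion, is by burn centre.

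**The concern.** An outpatient on the scan day contributes no bed-days from then on unless admitted later, while an inpatient contributes all remaining days of the stay. Hospital-day cost inherits the same split. A plain two-group comparison puts this gap between settings into the error term, although setting was known before the envelope was opened and is held in the hospital records from which the trial draws its data.

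The cost difference carries weight in this trial. The Background names shorter stay as a route to savings. If healing time and quality of life do not differ, the Economic evaluation section falls back on a cost-minimisation analysis, and the cost difference is then the whole economic answer. The sample size was set for healing time alone, so with 200 patients the choice of analysis is the main remaining means of sharpening the cost estimate.

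**Working it through.** **Plan's own figure.** There is none to reproduce: the protocol states no power or precision for length of stay or costs. The total of 200 is used below only as the reference size.

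**Assumed inputs.** The protocol gives no inpatient share, no variance for stay and no variance for cost. All inputs below are therefore assumptions, shown as ranges.

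**Formula.** Let *q* be the inpatient share at randomisation. The share of variance explained by setting is

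R² = q(1−q)(difference in setting means)² / total variance.

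The adjusted interval is √(1−R²) times as wide as the unadjusted one. The unadjusted trial size giving equal precision is 200/(1−R²). This describes the interval for a difference in means, not the rank test.

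**Length of stay.** Scale the inpatient mean to 1 and let *c* be the inpatient coefficient of variation. If outpatients stay at zero, R² = (1−q)/(c² + 1−q). The second and fourth rows let 10% of outpatients be admitted later, with half the inpatient mean and the same *c*. The outpatient mean is then 0.1 × 0.5 = 0.05, and the outpatient variance is 0.1 × 0.25 × (1+c²) − 0.05².

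| q | c | Late admissions | R² | Interval narrower by | Equivalent N |
|---|---|---|---|---|---|
| 0.5 | 1.0 | 0% | 0.5/1.5 = 0.33 | 18% | 300 |
| 0.5 | 1.0 | 10% | 0.2256/(0.2256+0.5238) = 0.30 | 16% | 286 |
| 0.2 | 0.6 | 0% | 0.8/1.16 = 0.69 | 44% | 644 |
| 0.9 | 1.3 | 10% | 0.0812/(0.0812+1.5275) = 0.05 | 3% | 211 |

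The last two rows are the extremes over q = 0.2–0.9, c = 0.6–1.3 and 0–10% late admissions.

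**Total cost.** Outpatients have real costs, so let their mean be *r* times the inpatient mean, with the same *c* in both settings:

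R² = q(1−q)(1−r)² / [q(1−q)(1−r)² + c²(q + (1−q)r²)].

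| q | r | c | R² | Interval narrower by | Equivalent N |
|---|---|---|---|---|---|
| 0.5 | 0.35 | 1.0 | 0.1056/(0.1056+0.5613) = 0.16 | 8% | 238 |
| 0.2 | 0.2 | 0.7 | 0.1024/(0.1024+0.1137) = 0.47 | 27% | 380 |
| 0.8 | 0.5 | 1.3 | 0.0400/(0.0400+1.4365) = 0.03 | 1% | 206 |

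The last two rows are the extremes over q = 0.2–0.8, r = 0.2–0.5 and c = 0.7–1.3.

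**Chance imbalance.** With 100 per arm and simple randomisation, the difference in inpatient share between arms has SD √(2q(1−q)/100), which is 5.7 percentage points at q = 0.2 or 0.8 and 7.1 at q = 0.5. With an assumed inpatient mean of 10 days and q = 0.5, one SD moves the difference in mean stay by 0.071 × 10 = 0.7 day.

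This is not a further loss. With c = 0.8, the unadjusted standard error is √(2(0.5×64 + 0.25×100)/100) = 1.07 days and the adjusted one is √(2×0.5×64/100) = 0.80. Since √(1.07² − 0.80²) = 0.71, the imbalance is exactly what the wider unadjusted interval already allows for.

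**The case against.** **Nothing stated is wrong.** Under randomisation and intention to treat, the unadjusted comparisons are unbiased. Length of stay and costs are secondary, and the primary outcome is untouched. This stands, and the point is limited to efficiency.

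**A fuller plan may add covariates.** It may. But the article names the tests and the ratio formula, and all are unadjusted. The sensitivity analysis it announces concerns the effect of statistical uncertainty on cost-effectiveness; it names no baseline adjustment.

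**Setting dominates both outcomes and much cost precision is lost.** A reader might infer this from the split in bed-days, but the protocol does not support it. A calculation that sets every outpatient to zero fits stay or bed cost only. Outpatients also incur costs for dressings, visits, travel and lost productivity. In the ranges above, setting explains 3–47% of total-cost variance, never more than half.

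**The inpatient share may be high.** The Sample size section reasons from admitted patients. At q = 0.9 and c = 0.8 with no late admissions, R² for stay is 0.1/0.74 = 0.14, and the equivalent size is only 231. This stands: the gain could be small.

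**Stratification may already balance setting.** To the extent that centre and burned surface area predict admission, the imbalance is smaller than computed. But the named comparisons ignore those factors as well, so the precision bought by stratifying does not reach the intervals. Adjusting for setting alone would be incomplete, and so would adjusting only the cost side of a ratio.

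**Conclusion.** The point holds as an improvement in precision. The plan compares stay and costs, and forms its ratios, without a baseline fact that is known before allocation, already on record, and likely to be strongly prognostic for stay and the hospital-day part of costs.

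The likely gain is moderate to large for length of stay and modest for total cost, where the mid-range case is an interval about 8% narrower. The full ranges, 3–44% and 1–27%, rest wholly on assumed inpatient shares, coefficients of variation and outpatient costs. They cover setting alone; any gain from centre and burned surface area is not included. The documents do not allow a single figure, and they do not support a reading that the planned comparison is biased.

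**What to change.** In the Statistical analysis section:

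1. Estimate the between-arm difference in mean length of stay and in mean total cost, both from randomisation, with a pre-specified linear model. It contains arm, care setting on the day of randomisation, centre, and burned-surface stratum (≤10% or >10%). Give bootstrap 95% intervals.
2. Record care setting before the envelope is opened, so that allocation cannot influence it.
3. For the cost-effectiveness and cost-utility ratios, adjust the cost difference and the effect difference for the same covariates. Bootstrap the two jointly by resampling patients, so that numerator and denominator are treated alike and their correlation is kept.
4. Keep the unadjusted results as a supporting table.

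The cost is a few lines of text and slightly more analysis work. No extra patients or procedures are needed. Setting should be obtainable from the patient records and hospital administration that the trial already uses. Fixing the covariates before results are seen also avoids any suggestion that they were chosen in response to an observed imbalance.
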